**Table 3. Best overall response**

| Response: First time point | Subsequent time point | BEST overall response                                           | Also requires                                       |
|----------------------------|-----------------------|-----------------------------------------------------------------|-----------------------------------------------------|
| CR                         | CR                    | CR                                                              | Normalization of tumor markers, tumor nodes < 10 mm |
| CR                         | PR                    | SD, PD or PR (see comment*)                                     |                                                     |
| CR                         | SD                    | SD provided minimum criteria for SD duration met, otherwise, PD |                                                     |
| CR                         | PD                    | SD provided minimum criteria for SD duration met, otherwise, PD |                                                     |
| CR                         | NE                    | SD provided minimum criteria for SD duration met, otherwise NE  |                                                     |

|                                                                                                                                                           |    |                                                                 |  |
|-----------------------------------------------------------------------------------------------------------------------------------------------------------|----|-----------------------------------------------------------------|--|
| PR                                                                                                                                                        | CR | PR                                                              |  |
| PR                                                                                                                                                        | PR | PR                                                              |  |
| PR                                                                                                                                                        | SD | SD                                                              |  |
| PR                                                                                                                                                        | PD | SD provided minimum criteria for SD duration met, otherwise, PD |  |
| PR                                                                                                                                                        | NE | SD provided minimum criteria for SD duration met, otherwise NE  |  |
| NE                                                                                                                                                        | NE | NE                                                              |  |
| * may consider PR providing initial “CR” likely PR on subsequent review – then original CR should be corrected. Recurrence of lesion after true CR is PD. |    |                                                                 |  |

## 9 Statistical considerations

### 9.1 Statistical design

This is an investigator-initiated single arm phase II study to investigate the activity of atezolizumab in combination with carboplatin in metastatic ILC. In order to minimize the expected number of patients treated in the event that the regimen proves to be very disappointing or very successful, a two-stage design will be used for patient accrual.[22]

### 9.2 Sample size

For metastatic ILC patients who are refractory to endocrine treatment, no first or second line 'standard' therapies have been defined. Frequently used anticancer agents are capecitabine, or a taxane. The median PFS reached with these therapies typically lies between 2-4 months, but limited data are available. [25, 26] For this study, it is determined that a regimen that is likely to yield a proportion of patients that is free of progression at 24 weeks of more than 25% should be further explored in a randomized study.

Simon's two-stage (minimax) design will be used.[22] The null hypothesis that the true proportion of patients that is free of progression at 24 weeks is  $\leq 10\%$  will be tested against a one-sided alternative of at least 25%. In the first stage, 22 patients will be accrued. If there are 2 or fewer patients free of progression at 24 weeks in these 22 patients, the study will be stopped or another immunomodulatory drug will be added (agent to be determined). Otherwise, 18 additional patients will be accrued for a total of 40. The null hypothesis will be rejected if 8 or more patients out of those 40 are free of progression at 24 weeks. This design yields a type I error rate 0.04 and power of 80% when the true proportion of patients free of progression at 24 weeks is 25%.

In conclusion, in the run-in phase I part six patients will be included (3+3). In the first stage 22 (including the first n=6 from the run-in phase I part) patients will be included. If 3 or more patients are free of progression at 6 months (see statistics section below), an additional 18 subjects will be entered. Total= 22+18=40. For evaluation of efficacy according to the Simon's two-stage design we will use all patients who received at least 1 cycle of atezolizumab (per protocol population).

### 9.3 Accrual and duration of study

At least 40 patients will be included. The trial will open at the Netherlands Cancer Institute plus 3 academic hospitals in the Netherlands. We estimate that the Netherlands Cancer Institute will accrue 20 patients in two years' time. And for the other centers we expect to include 10 patients/center in two years' time. The estimated duration of the study is two years.

### 9.4 Statistical analysis populations

The following analysis populations will be used for the analysis of the trial:

- ◆ **Per protocol population:** All patients who have received at least one dose of atezolizumab.
- ◆ **Safety population:** All patients who have started on carboplatin.

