| Primary endpoint     | Proportion of patients who remain free of progression (time from start carboplatin to tumor progression or death from any cause) at 6 months. Progression as defined by RECIST 1.1 [16] will be used.                                                                                                                                                                                                                                                                                                                                                                                                                                                                                                                                                                                                                                                                                                                                                                                                                                                                                                                                                                                                                                                                                                                                                                                                                                                                                                                                                                                                                                                                                                                                                                                                                                                                                                                                                                                                                                                                                                                                                                                                                                                                                                                                                                                                                                                                                                                                                                                                                                                                                                                                                                                                                                                                                                                                                                                                                                               |

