#### 7.2.2 Before start atezolizumab cycle 1/carboplatin no 3 (cycle 1, day 1)

- ◆ Collect fresh biopsies of a metastatic lesion for FFPE and frozen tissue. Biopsies preferably taken from the lesion biopsied at baseline taking into account the risk of complications during the

procedure and sufficient volume of the lesion in case of objective response. Collect 3x16 G biopsies (1 for FFPE and 2 for frozen).

- ◆ Tumor measurements by CT scan thorax/abdomen
- ◆ Symptom directed physical exam
- ◆ Adverse events of grade  $\geq 2$
- ◆ Laboratory testing: hematology (Hb, leukocytes and differentiation, platelets), biochemistry (glucose, creat, urea, sodium, potassium, magnesium, chloride, calcium, phosphate, albumin, bilirubin,  $\gamma$ GT, AF, AST, ALT, LDH, CRP, TSH, free T4, amylase, lipase, ACTH, cortisol, FSH, LH, E2), CA15.3, CEA
- ◆ Blood samples for biobanking (translational research purpose).
- ◆ Collect stool sample for microbiome analysis (optional)

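### The primary endpoint is timed from carboplatin, but only patients dosed with atezolizumab about two weeks later are analysed, so undosed early failures drop out and can only push the progression-free proportion up

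*Protocol*

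**What the plan says.** **Clock.** The Synopsis defines the primary endpoint through "time from start carboplatin to tumor progression or death from any cause", assessed at 6 months. Section 3.4 repeats the endpoint without a starting point. Section 9.2 states the hypotheses and decision rules at 24 weeks. That difference is a separate matter, and the 24-week wording is used here.

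**Treatment sequence.** Carboplatin is given weekly. Atezolizumab is added after two administrations, about two weeks in (4.1 and the table in 7.5).

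**Analysis set.** Section 9.4 defines the per protocol population as "All patients who have received at least one dose of atezolizumab". Section 9.5 uses it for all efficacy analyses, including the primary proportion. Sections 4.1 and 9.2 and the Synopsis use it for the Simon evaluation, and the Synopsis adds that all 22 first-stage patients must have had at least one atezolizumab cycle. Everyone who starts carboplatin forms the Safety population, which is used for safety only.

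**Assessment in the gap.** Section 7.2.2, before the first atezolizumab dose, lists "Tumor measurements by CT scan thorax/abdomen". Section 8.1 compares measurements with screening. Sections 6.1.5 and 7.3 take patients off study at progression, with an exception in 8.1 and 8.2 for treatment beyond initial progression.

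The protocol nowhere counts a progression or death before atezolizumab as a failure in the primary analysis.

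**The concern.** Time zero and entry to the denominator are about two weeks apart, and the event being counted can decide whether a patient enters. A death during induction is a primary event under the Synopsis definition, yet that patient can never join the analysed set. The same holds for a patient whose progression is found on the CT before atezolizumab, or clinically, and who is then not dosed. Each such exclusion removes a failure from the denominator and nothing from the numerator.

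At stake are both decisions of the trial: passing the first stage with 3 or more of 22, and rejecting the null with 8 or more of 40. Both become easier to reach with no effect of treatment. The reported proportion also describes a more favourable group than the one in which the clock started.

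**Working it through.** **Inputs from section 9.2.** Null proportion 10%; one-sided alternative 25%; stop at 2 or fewer of 22; 18 further patients; reject at 8 or more of 40; stated type I error 0.04 and power 80%.

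**Input not in the protocol.** The share d of carboplatin starters who fail before atezolizumab and are not dosed. It is assumed, over a range of 0% to 10%.

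**Step 1: the plan's own figures.** For a proportion p in the analysed set,

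P(reject | p) = sum over x = 3 to 22 of C(22, x) p^x (1 − p)^(22 − x) × P[Bin(18, p) ≥ 8 − x].

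- p = 0.10: 0.0398, with probability 0.620 of stopping after stage one.
- p = 0.25: 0.8032.

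The stated 0.04 and 80% are reproduced. The design arithmetic is correct.

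**Step 2: effect of the exclusion.** Of N starters, pN are progression-free at 24 weeks, and all of these are taken to have been dosed. The dN early failures are left out. The analysed proportion is therefore pN / (N − dN) = p / (1 − d).

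**Step 3: the same rule at the shifted proportion.**

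| Early failures left out (assumed) | True 10% is analysed as | Type I error | True 25% is analysed as |
|---|---|---|---|
| 0% | 10.0% | 0.040 | 25.0% |
| 2.5% | 0.10/0.975 = 10.3% | 0.045 | 25.6% |
| 5% | 0.10/0.95 = 10.5% | 0.051 | 26.3% |
| 10% | 0.10/0.90 = 11.1% | 0.067 | 27.8% |

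**Step 4: in patient counts.** Suppose 8 of 40 dosed patients are progression-free.

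- No early failure left out: 8/40 = 20.0%; single-stage exact one-sided p against 10% is 0.042.
- Two left out: 8/42 = 19.0%, p = 0.054.
- Four left out: 8/44 = 18.2%, p = 0.068.

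**Step 5: scale.** Section 9.2 gives a median PFS of 2 to 4 months on usual therapy. If PFS were exponential (an assumption), the share of events in the first two weeks would be 1 − 0.5^(0.46/m) with m in months: 14.7% for m = 2 and 7.7% for m = 4. These are not estimates of d, because an early event removes a patient only if it is fatal or detected and no atezolizumab follows.

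**The case against.** The best defence is that this is a choice of estimand. The objective concerns the combination, and a patient who leaves after one or two carboplatin doses never received it. The restriction is fixed in advance and stated consistently. Some patients may leave for reasons unrelated to outcome, such as withdrawing consent or declining the second biopsy, and counting all of these as failures would bias downward. For a target defined as patients who reach atezolizumab, with 10% as the null for that group, the 0.04 is exact.

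Part of this stands. An atezolizumab-treated set can be a sound primary population, but the clock and the null must then belong to it. Here the clock starts earlier and no rationale ties the 10% to that set. Patients who leave without progression need a rule of their own, given under the fix.

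A reader might also infer more than the protocol supports:

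- *That the first two weeks are event-free by construction.* They are not. Exclusion depends on not being dosed. Section 8.1 places the first official response evaluation after four atezolizumab cycles, and 8.2 allows treatment beyond initial progression while dating the event at that first progression. A patient with early progression who is still dosed stays in as a failure.
- *That the 10% null came from data on all treated patients, timed from start of treatment.* Section 9.2 cites a median PFS and states 10% without deriving it.
- *That the error more than doubles.* A figure of 0.093 needs 16% of starters to be lost, which follows from a constant hazard reaching 10% at 6 months. That implies a median of 6 × ln 2 / ln 10 = 1.8 months, below the protocol's own 2 to 4 months, and requires every early event to be found and none of those patients dosed.
- *That there is an explicit replacement rule.* The Synopsis requires atezolizumab for the first 22. For the full 40 it follows only from the population definition.

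**Conclusion.** The mismatch is in the text and its direction is certain: leaving out undosed patients who progressed or died can only raise the progression-free proportion. Its size is not known. It is zero if every starter is dosed or no undosed leaver has failed. If about 5% of starters are lost as early failures, roughly 2 of 42, the type I error for the carboplatin-start endpoint passes 0.05; at 10% it is 0.067.

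These figures assume a true 10% among all starters and that every excluded patient is a failure. The stated 0.04 is not a miscalculation. It applies to the endpoint as the Synopsis defines it only when no early failure is lost. The change is worth making because the bias runs one way, the needed population already exists in the protocol, and only wording is involved.

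**What to change.** In 4.1, 9.2, 9.4 and 9.5, and in the matching Synopsis entries:

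- Make all patients who start carboplatin the primary efficacy set. Apply the 3/22 and 8/40 rules to the first 22 and the first 40 of them.
- Count progression or death before atezolizumab as not progression-free.
- Keep patients who leave induction without progression in the set and follow them by CT to progression. Section 7.2.6 already asks for this when a patient goes off study for another reason. It sits under the heading for atezolizumab cycle 4 onwards, so say expressly that it covers induction. Count those with no 24-week status as not progression-free, with a sensitivity analysis that excludes them.
- Report the atezolizumab-treated set as supportive, and give the number of patients lost during induction with reasons.
- State the start of the clock in 3.4 as well as in the Synopsis.

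Applied to starters, the rule has type I error 0.0398 at 10% and power 0.8032 at 25%.

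Alternatively, if the atezolizumab-treated set stays primary, start the clock at the first atezolizumab dose and justify the 10% null for that population.

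The cost is wording, plus a few patients in the denominator who never received atezolizumab, so the observed rate is slightly lower. If the 25% was meant for dosed patients and 5% of starters are lost as failures, the starters' rate is 0.25 × 0.95 = 23.75%, and the step 1 formula gives power 0.75. The sponsor should say which group the 25% describes.

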### 3.2 Secondary Objective

- To evaluate the outcome after atezolizumab together with carboplatin in the IR-profile subgroup vs the non-IR-subgroup as defined by gene expression profiling (retrospectively defined as previously described [9])
- To evaluate the safety of atezolizumab together with carboplatin
- To evaluate the efficacy of atezolizumab plus carboplatin using objective response rate
- To evaluate the efficacy of atezolizumab plus carboplatin using proportion of patients free of progression at 12 months
- To evaluate the efficacy of atezolizumab plus carboplatin using overall survival
- To explore the role of potential biomarkers to predict response to atezolizumab plus carboplatin

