### 3.4 Endpoints

The primary endpoint is:

Proportion of patients who remain free of progression at 6 months. Progression as defined by RECIST 1.1 [34] will be used.

The secondary endpoints are:

- Proportion of patients free of progression (RECIST 1.1[34]) at 6 months in the IR-profile subgroup vs the non-IR-subgroup as defined by gene expression profiling(retrospectively defined as previously described [9])
- Proportion of patients who remain free of progression at 12 months. Progression as defined by RECIST 1.1 [34] will be used.
- Progression as defined by iRECIST [17]
- Overall survival

- Percentage of patients with toxicity (according to CTCAE v4.03, Appendix A) and immune-related toxicity defined as the Adverse Events of Special Interest (AESI's) for atezolizumab (see section 6 and Investigator's Brochure for atezolizumab)
- Objective response rate (RECIST 1.1[34])

*The exploratory endpoints are listed in Section 10 Translational Research*

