#### 7.2.3 During weekly carboplatin administration (day 8 and 15 of cycle 1,2 and 3)

- ◆ Symptom directed physical exam
- ◆ Adverse events of grade  $\geq 2$  and the Adverse Events of Special Interest for atezolizumab
- ◆ Laboratory testing: hematology (Hb, leukocytes and differentiation, platelets), biochemistry (creat, urea, sodium, potassium, calcium, albumin, bilirubin,  $\gamma$ GT, AF, AST, ALT, LDH).

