### 9.5. Statistical methods

Efficacy analyses will be done using the **Per protocol population**. Safety analyses will be performed on the **Safety population**.

- ◆ Frequency tables will be tabulated (by treatment group or otherwise) for all categorical variables by the levels of the variables. Continuous variables (for example age, dose etc) are presented using the

median and range (minimum, maximum) or mean (variance) depending whether the distribution appears symmetrical.

- ◆ Baseline demographic characteristics of the **Per protocol population** will be summarized according to common reporting standards (following CONSORT-guidelines 2010, where applicable). Proportions will be presented together with 85% as well as 95% confidence intervals (CIs).
- ◆ Description of number of cycles of therapy and dose modifications for both the induction treatment as well as the treatment with atezolizumab (**Per protocol population**)
- ◆ Activity of atezolizumab plus carboplatin will be studied in the **Per protocol population** as described above by calculating the proportion of patients free of progression at 24 weeks (PFS according to RECIST (primary endpoint)). Spiderplots and swimmerplots will be used to illustrate the magnitude and duration of response.
- ◆ Activity of atezolizumab will be studied in the **Per protocol population** as described above by calculating ORR and clinical benefit (secondary endpoints) as defined by RECIST. Proportions will be presented together with 85% as well as 95% confidence intervals (CIs).
- ◆ Safety analyses will be performed on the **Safety population**. The worst toxicity grade over all cycles according to the CTCAE criteria version 4.03 will be displayed.
- ◆ For exploratory analyses, means will be compared using either student t-test if validity conditions are fulfilled or using non parametric Wilcoxon-Mann-Whitney tests. Proportions will be compared using either Chi2 statistics or Fisher's exact test depending on validity conditions.

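### Section 9.5 gives two descriptive safety outputs the wrong population: atezolizumab AESIs are counted over all carboplatin starters, and induction exposure only over patients who reached atezolizumab

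*Protocol*

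**What the plan says.** Section 9.4 of the protocol defines two populations. The Safety population is "All patients who have started on carboplatin". The Per protocol population is "All patients who have received at least one dose of atezolizumab".

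Section 9.5 then assigns them:

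- **Safety.** "Safety analyses will be performed on the" Safety population, and "The worst toxicity grade over all cycles according to the CTCAE criteria version 4.03 will be displayed". No exception is made for any safety endpoint.
- **Exposure.** "Description of number of cycles of therapy and dose modifications for both the induction treatment as well as the treatment with atezolizumab" is assigned to the Per protocol population, so one population serves both treatment phases.

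Section 3.2 lists as a secondary objective "To evaluate the safety of atezolizumab together with carboplatin". Section 3.4 includes among the secondary endpoints the percentage of patients with toxicity and with "immune-related toxicity defined as the Adverse Events of Special Interest (AESI's) for atezolizumab".

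Under Section 4.1, atezolizumab starts only after two carboplatin administrations. Section 7.2.2 places a biopsy and a CT scan before the first atezolizumab dose. The visit list in Section 7.2.3 (day 8 and 15 of cycles 1 to 3) adds to the grade 2 or higher adverse events "and the Adverse Events of Special Interest for atezolizumab". The visit lists for induction day 8 (7.2.1) and for the visit before cycle 1 (7.2.2) do not carry that item.

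**The concern.** The two populations differ by exactly those patients who start carboplatin and never receive atezolizumab. The protocol allows for such patients: the synopsis requires all 22 stage 1 patients to have had at least one cycle of atezolizumab, and Section 9.3 speaks of at least 40 inclusions.

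These patients are placed badly twice. In the AESI percentage they count in the denominator although they were never exposed to the drug whose special-interest events are being counted, which tends to lower the figure. In the description of induction they are left out, although they are the patients who say most about whether induction leads on to the combination.

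At stake is how readable two descriptive outputs are. The protocol states in Section 4.2 that atezolizumab had not been given with carboplatin at this dose level, so readers will look to the AESI percentage for the experience of patients who actually received the combination.

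**Working it through.** **The plan's own figure.** The only computed design figure is the Simon two-stage rule in Section 9.2: stop at 2 or fewer of 22, reject at 8 or more of 40. The exact two-stage binomial gives a type I error of 0.0398 (stated 0.04) and power of 0.803 (stated 80%). It reproduces and does not depend on the point made here.

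**Inputs for the AESI percentage**

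- Atezolizumab-treated patients: 40, the planned total in Section 9.2.
- k, the number who start carboplatin but never receive atezolizumab: not given. Assumed 0 to 10, taken as additional to the 40.
- AESI rate: not given. 30% (12 of 40) and 20% (8 of 40) are used for illustration.

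**Formula.** Let a be the AESI proportion in the 40 treated and b the proportion of the k early leavers with an AESI-list event during induction. The Safety population figure is

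(40a + kb) / (40 + k).

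If b = 0 this is a × 40/(40 + k). If b lies between 0 and a, the dilution is smaller. If b = a, there is none.

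**Results with b = 0**

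| k | factor 40/(40+k) | 12 AESI patients | 8 AESI patients |
|---|---|---|---|
| 0 | 1.000 | 30.0% | 20.0% |
| 2 | 0.952 | 12/42 = 28.6% | 8/42 = 19.0% |
| 4 | 0.909 | 12/44 = 27.3% | 8/44 = 18.2% |
| 6 | 0.870 | 12/46 = 26.1% | 8/46 = 17.4% |
| 10 | 0.800 | 12/50 = 24.0% | 8/50 = 16.0% |

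**With b above 0.** For k = 4 and one early leaver with an AESI-list event, the figure is (12 + 1)/44 = 29.5%, close to the 30.0% in treated patients.

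**Induction exposure.** Suppose all 40 Per protocol patients had both induction doses, so that population shows 100%. If the k early leavers had only one dose, the figure over all starters is 40/42 = 95.2%, 40/44 = 90.9% or 40/46 = 87.0% for k = 2, 4, 6. If they had both doses, it stays at 100%. The induction figures therefore move only if early leavers had fewer doses or more modifications than the rest.

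**The case against.** The strongest reply is that everyone who started study treatment is a sound safety population for a regimen whose induction is part of it. Section 9.5 never names AESIs, so their denominator is inferred from a general sentence, and an extra column for atezolizumab-treated patients is often left to an SAP. The first part stands for overall toxicity, and the fix keeps that population there. The second does not dispose of the point, because the protocol itself fixes both assignments without an exception.

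Several stronger readings are tempting, and here the reply succeeds:

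- **A reader might infer that early leavers cannot contribute an AESI.** Section 3.4 defines the endpoint by the AESI list, not by attribution to atezolizumab. The list in Section 6.1.2 includes hypoxemia, hepatitis, transaminitis and events suggesting hypersensitivity, and Section 6.3.2 itself provides for carboplatin hypersensitivity. Grade 2 or higher events are collected at the induction visits, and Section 11.4 records all adverse events after first study medication. Few or no AESIs is a fair expectation; none is an assumption.
- **A reader might derive the early-leaver share from the 2 to 4 month median PFS in Section 9.2.** With a constant hazard, 1 − exp(−ln2 × 2/(m × 4.348)) gives 14.7%, 10.1% and 7.7% progressing or dying by week 2 for m = 2, 3, 4 months. But those medians come from other therapies, and nothing in the protocol says that the CT before cycle 1 bars atezolizumab. Section 8.1 places the first official response evaluation after four atezolizumab cycles.
- **A reader might conclude that induction stopping is reported as 0% and induction tolerability overstated.** Section 9.5 plans no discontinuation rate. Both induction doses fall on days 1 and 8 (Section 7.5), so a patient whose progression is found before cycle 1 would normally have had both. Induction toxicity is already analysed in all carboplatin starters. A patient who stops only carboplatin for toxicity may continue on atezolizumab (Section 4.1) and so can stay in the Per protocol population.

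The shift is also well inside sampling error: the exact 95% interval for 12 of 40 is about 17% to 47%.

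**Conclusion.** The point holds as a minor one. Followed as written, Section 9.5 measures atezolizumab AESIs over some patients who may never have received atezolizumab, and describes induction without the patients who left before atezolizumab.

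The first effect lowers the AESI percentage whenever k is above 0 and AESI-list events are rarer in early leavers than in treated patients. It is about 1 to 4 percentage points on a 30% rate for k = 2 to 6, if early leavers have no such event. The second removes a relevant group from the description, but changes the figures only if that group had fewer doses or more modifications. Both vanish if every patient reaches atezolizumab.

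These sizes rest on assumed values of k and of the AESI rate; the protocol gives neither. The documents do not support a claim that the regimen's safety is materially misrepresented, or a specific early-leaver share. The primary endpoint, sample size, type I error, power and DLT rule are unaffected.

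**What to change.** Change two assignments in Section 9.5, using the populations already defined in Section 9.4:

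1. Report the AESI (immune-related toxicity) percentage with patients who received at least one dose of atezolizumab as denominator. Keep the Safety population for overall toxicity from the first carboplatin dose.
2. Describe induction doses, cancelled doses and the number who did not go on to atezolizumab in the Safety population. Keep the atezolizumab-treated population for atezolizumab exposure.

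The cost is two wording changes and one extra table column, with no new data, visits or patients. The one downside for the presentation is that the AESI percentage may come out slightly higher.
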